**Fig. 2 Fig2:**
[figure not shown]
Schematic illustration of the research design. Ht, height; Wt, weight; WC, waist circumference; RHR, resting heart rate; RBP, resting blood pressure; SaO_2_, resting oxygen saturation; EF, endothelial function; INS, blood insulin; GLU, blood glucose; LMPP, lipoprotein metabolism profile; HbA1C, glycosylated hemoglobin; DEXA, dual X-ray absorptiometry; HIFT, high-intensity function training; PACES, exercise enjoyment questionnaire; EIQ, Exercise Intention Questionnaire; IFIS, International Fitness Scale

**Table 3 Tab3:**
[figure not shown]
Schedule of the study period

*HIFT* high-intensity functional training

*Each time point represents one week

#### Sample size {14}

The sample size was projected with a change in ApoB as the main outcome variable between HIFT1 and HIFT3. Power calculations (IBM SPSS v25 Armond, NY) assumed a 1:1 equal allocation between HIFT1 and HIFT3. The baseline mean and standard deviations from a previous study [97] and pilot studies for ApoB were ~ 129 ± 25 mg/dL in sedentary adults with elevated cardiometabolic risk. Collectively, using these data, we consider a 15% reduction in ApoB to be clinically meaningful within the HIFT3 group [98]. Assuming a power of 0.90, *α* = 0.05, and an effect size of *d* = 0.80, a paired samples one-tailed *t*-test sample size calculation revealed a sample size of 60 subjects (20 per group) will establish the superiority of HIFT3 versus HIFT1 for pre- to post-differences in the primary outcome ApoB. With an estimated 5% dropout rate, we will recruit 22 subjects/group to obtain the necessary sample size of 60. Therefore, a total of 60 men and women who meet the previously stated inclusion criteria will be recruited and randomized post-baseline assessments into one of the three intervention groups. Data will be collected in cohorts of 12, randomized into intervention groups. This will continue until 20 participants per intervention group have completed the study. This will accommodate dropout within cohorts.

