### Outcomes {12}

#### Primary outcomes

##### Blood analysis

Baseline and post-training blood analysis will be measured via venipuncture of the antecubital vein. Five milliliters of blood will be drawn for the lipoprotein metabolism profile (LMPP), 1 mL will be drawn for insulin, 1 mL will be drawn for glucose, 1 mL will be drawn for HbA1c, and 1 mL will be drawn for hematocrit. The LMPP consists of an ApoB count, Lp[a] count, and cholesterol and triglyceride content of each lipoprotein subclass (VLDL, LDL, HDL). Hematocrit is calculated to adjust for plasma volume changes applied to the cholesterol and triglyceride content measures. Glucose and insulin measures will be used to calculate insulin resistance (IR) using the homeostatic model assessment (HOMA) [83, 84]. For each variable, individual change from baseline will be calculated. Data will be aggregated as mean ± standard deviation (SD) for each dose group as well as for male and female subgroups with each dose groups. The mean change ± SD for each variable will be compared between the 3 dose groups and subgroups.

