## Statistical methods

### Statistical methods for primary and secondary outcomes {20a}

Only data from participants who complete ≥ 80% of total exercise intervention and with no noticeable change in eating (statistically different energy consumption and macronutrient distribution) and physical activity habits will be included [97, 99, 100]. All data will be analyzed using the Statistical Package for the Social Sciences (IBM SPSS v25, Armond, NY). Descriptive data if normal will be presented as mean ± SD, or median and interquartile range if not normal; the significance level of all comparative data will be set as *p* ≤ .05, and normality will be assessed using a Kolmogorov-Smirnov test. If normality exists, parametric tests will be used, if normality does not exist, non-parametric tests will be used. Effect sizes (ES) and confidence intervals (CI) will be calculated on the results of all dependent variables. Paired *t*-tests will be used to evaluate the significant differences between pre- and post-measures of both primary and secondary physiological outcomes within each group. A one-way ANOVA will be used to compare the primary and secondary outcomes pre-post mean change between the three groups. When indicated by a significant *F* value, post hoc analysis will be determined using the Bonferroni adjustment for multiple comparisons. The median, mode, and interquartile ranges of the IFIS and PACES data will be calculated for each of the three groups. Should missing data in outcomes occur, a linear-mixed model will be conducted instead of ANOVA as this test accounts for missing data.

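### The stated 90% power for ApoB change (HIFT3 versus HIFT1) is supported only by a baseline between-person SD; with no SD of change, power at 20 per arm is not established

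*Protocol article*

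**What the plan says.** The Sample size section names the contrast and the outcome: "The sample size was projected with a change in ApoB as the main outcome variable between HIFT1 and HIFT3". The variability it reports is a baseline figure: "The baseline mean and standard deviations from a previous study [97] and pilot studies for ApoB were ~ 129 ± 25 mg/dL". The target follows, as a reduction inside one arm: "we consider a 15% reduction in ApoB to be clinically meaningful within the HIFT3 group". The section then sets power at 0.90, alpha at 0.05 and d at 0.80, and reports that "a paired samples one-tailed *t*-test sample size calculation revealed a sample size of 60 subjects (20 per group") is enough to show HIFT3 superior to HIFT1.

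The analysed quantity is within-person change. Under Outcomes, Blood analysis: "For each variable, individual change from baseline will be calculated". Under Statistical methods for primary and secondary outcomes: "A one-way ANOVA will be used to compare the primary and secondary outcomes pre-post mean change between the three groups". Paired t-tests appear there only for pre-post comparisons within each arm. No SD of ApoB change and no pre-post correlation appears in the document.

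**The concern.** For a comparison of mean change between arms, the standardised effect is the between-arm difference in change divided by the SD of change. The SD of single baseline values is a different quantity. Change can vary less or more than baseline values do, depending on how closely a person's two measurements agree. The protocol supplies only the baseline SD, and the numbers fit its having been used as the denominator.

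HIFT3 versus HIFT1 on ApoB is the sole basis for 20 per arm. If the SD of change is unknown, so is the power of that comparison, and a null result cannot be told apart from a trial that was too small. Correcting only the type of test would leave this input unsupported.

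**Working it through.** **Inputs from the Sample size section.** Mean 129 mg/dL, baseline SD 25 mg/dL, 15% target, d = 0.80, alpha 0.05, power 0.90, paired one-tailed t-test, 20 per arm.

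**Assumptions not in the document.** (a) Pre and post SDs are both 25. (b) The whole 15% fall is the between-arm difference, so HIFT1 does not change. (c) r ranges from 0.3 to 0.8.

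**Step 1: the protocol's own figure.** For a paired one-tailed t-test at d = 0.80 and alpha 0.05, the noncentral t distribution gives 90% power at n = 15, not 20. At n = 20 the same test has 96% power. A paired two-tailed test gives n = 19 at d = 0.80 and n = 20 at d = 0.774. So 20 per group does not reproduce as stated.

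**Step 2: where d may come from.** 0.15 × 129 = 19.35 mg/dL, and 19.35/25 = 0.774. Also 20/25 = 0.80. The stated d is therefore close to the target divided by the baseline SD, but the protocol does not show its derivation.

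**Step 3: SD of change.** With equal pre and post SDs, SD of change = 25 × √(2(1 − r)). This equals 25 only at r = 0.5. Without equal SDs the formula is √(25² + s² − 2r × 25 × s). At r = 0.5, a post SD s of 20 gives 22.9 and one of 30 gives 27.8.

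**Step 4: power at 20 per arm.** Here d = 19.35 / SD of change. For two independent arms the noncentrality is d × √(20/2) on 38 df. The last column applies the protocol's paired one-tailed formula (d × √20 on 19 df) to the same d, to separate the effect of the SD from that of the test.

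| r | SD of change | d | Two-sample, one-sided | Two-sample, two-sided | Paired, one-tailed |
|---|---|---|---|---|---|
| 0.3 | 29.6 | 0.65 | 65% | 52% | 88% |
| 0.5 | 25.0 | 0.77 | 78% | 66% | 95% |
| 0.7 | 19.4 | 1.00 | 93% | 87% | >99% |
| 0.8 | 15.8 | 1.22 | 98% | 96% | >99% |

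**Step 5: what 0.90 requires at 20 per arm.**

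- Two-sample, one-sided: d of at least 0.942, so an SD of change of at most 19.35/0.942 = 20.5 (r about 0.66).
- Two-sample, two-sided: d of at least 1.052, so at most 19.35/1.052 = 18.4 (r about 0.73).
- Paired one-tailed: d of at least 0.679, so at most 28.5 (r about 0.35).

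**Step 6: if d = 0.80 is already on the change scale.** At 20 per arm, two-sample power is 80% one-sided or 69% two-sided.

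**The case against.** The strongest reply is that nothing shows the baseline SD was the divisor. In a paired t-test d belongs to the difference scale by definition, 19.35/25 is 0.77 rather than 0.80, and 0.80 may be a conventional or separately assumed value. This stands: use of the wrong SD is an inference. It does not rescue the stated power, because the document gives no SD of change behind d, and Step 6 shows that a change-scale d of 0.80 still falls short of 0.90 between arms.

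A second reply is that the two-sample figures mix faults. This also stands. At r = 0.5 the SD of change is exactly 25 under the equal-SD assumption, so the SD contributes no error there. The drop to 78% or 66% then comes wholly from the independent-arms formula and the sidedness. On the paired one-tailed formula alone, power stays near or above 0.90 unless r is below about 0.35.

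A reader might infer from the table that the trial is underpowered because the wrong variance was used. The documents do not support that. They give no value of r, and the range runs from well below 0.90 to above it.

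**Conclusion.** The stated 0.90 is not established for the planned between-arm comparison of ApoB change. What can be said firmly is that the only SD given is on the baseline scale and that no change-scale figure supports d = 0.80. Under the equal-SD assumption and a full 19.35 mg/dL difference, power at 20 per arm runs from 65% to 98% one-sided, or 52% to 96% two-sided, for r between 0.3 and 0.8. Accepting d = 0.80 as it stands gives 80% or 69%.

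The direction of any error due to the SD alone is unknown. The 15% is defined within HIFT3, so if HIFT1 also improves, the between-arm difference shrinks and power is lower at every r. With an assumed 5% fall in HIFT1 (0.10 × 129 = 12.9 mg/dL difference), one-sided power is 48% at r = 0.5 and 66% at r = 0.7.

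**What to change.** In the Sample size section:

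1. State the SD of pre-to-post ApoB change, or r, with its source. The protocol credits the cited study and the pilot studies only with baseline figures, so first check whether they hold post values. If they do not, declare a range.
2. Define d as the assumed HIFT3 minus HIFT1 difference in change divided by that SD, and state what change is assumed in HIFT1.
3. Replace 0.90 with the power at 20 per arm from a two-sample formula at the sidedness planned for the analysis, given as a range if the SD is uncertain.

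The cost is a check of existing data, a short calculation and a few rewritten sentences. Restating the power does not itself change the sample size. Whether 20 per arm remains acceptable is a decision for the investigators once the figure is known.

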### Trial design {8}

The present study is a parallel-group, three-arm, exploratory, randomized, dose-response clinical trial. Randomization is at a 1:1:1 allocation ratio for the three arms.

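### The 20 per group comes from a paired one-tailed t-test, so the stated 90% power for HIFT3 versus HIFT1, a contrast of independent arms, is unsupported

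*Protocol article*

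**What the plan says.** All of the sizing is in the protocol article, Sample size {14}.

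- **Target comparison:** "The sample size was projected with a change in ApoB as the main outcome variable between HIFT1 and HIFT3". The calculation "assumed a 1:1 equal allocation between HIFT1 and HIFT3".
- **Inputs:** "Assuming a power of 0.90, *α* = 0.05, and an effect size of *d* = 0.80". Baseline ApoB is given as about 129 ± 25 mg/dL. No SD of change and no pre-post correlation are given.
- **Clinically relevant effect:** "we consider a 15% reduction in ApoB to be clinically meaningful within the HIFT3 group".
- **Method and result:** "a paired samples one-tailed *t*-test sample size calculation revealed a sample size of 60 subjects (20 per group").
- **Claim:** this number "will establish the superiority of HIFT3 versus HIFT1 for pre- to post-differences in the primary outcome ApoB".

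Two other sections bear on it. Trial design {8} describes parallel groups: "Randomization is at a 1:1:1 allocation ratio for the three arms". Statistical methods {20a} keeps paired t-tests for change within each group. For the comparison between groups it says: "A one-way ANOVA will be used to compare the primary and secondary outcomes pre-post mean change between the three groups". Bonferroni post hoc tests follow a significant F, at p ≤ .05, and no one-tailed test is mentioned there.

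**The concern.** A paired t-test asks whether one group's own change differs from zero. The superiority claim asks whether change in one set of people differs from change in another set. The second question carries sampling error from both arms, so at the same standardised effect it needs many more people per arm. The analysis section makes this distinction itself, which leaves the calculation at odds with both the comparison it is meant to power and the planned test.

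The stake is how a null result would be read. The trial looks for the smallest weekly dose that helps. If HIFT3 versus HIFT1 is not significant and 90% power is quoted, a reader may conclude that one session does as well as three, when a real difference may simply have been missed.

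**Working it through.** **Inputs from Sample size {14}:** power 0.90, α = 0.05, d = 0.80, 20 per group, baseline 129 ± 25 mg/dL, 15% reduction. Power is from the exact noncentral t distribution.

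**1. Reproducing the stated 20.** Paired test: noncentrality = d√n, df = n − 1.

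| Paired version | n for 90% | Power at n = 20 |
|---|---|---|
| One-tailed, d = 0.80 (as written) | 15 (14 gives 88.2%, 15 gives 90.3%) | 96.4% |
| Two-tailed, d = 0.80 | 19 | 92.4% |
| Two-tailed, d = 0.774 | 20 | 90.7% |

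The inputs as written give 15. The last row uses 0.15 × 129 = 19.35 mg/dL and 19.35 / 25 = 0.774. It returns exactly 20, but it is a two-tailed, within-group calculation.

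**2. The comparison actually claimed.** Independent groups: noncentrality = d√(n/2), df = 2n − 2. With n = 20 and d = 0.80 this is 0.80 × √10 = 2.530. Here d is taken as the between-arm difference in change over the SD of change.

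| Test at 20 per arm | Critical t | Power | n per arm for 90% |
|---|---|---|---|
| One-sided 0.05 (stated sidedness) | 1.686 | 79.9% | 28 |
| Two-sided 0.05 | 2.024 | 69.3% | 34 |
| Bonferroni, two-sided 0.05/3, df 38 | 2.505 | 51.6% | 44 |
| Bonferroni, two-sided 0.05/3, pooled df 57 | 2.467 | 52.9% | 44 |

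Simulating the full planned sequence (significant F, then the Bonferroni HIFT3–HIFT1 contrast; 100,000 runs; HIFT2 at 0, 0.4 or 0.8 SD) gives 52% to 53%. With 20 per arm, two-sided power reaches 90% only at d of about 1.05.

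**3. If d is on the baseline SD.** The protocol does not say how d = 0.80 arose. That 19.35 / 25 = 0.774 is close to 0.80 suggests scaling to the baseline SD, but this is an inference. With equal pre and post SDs and correlation r (assumed values), SD of change = 25√(2(1 − r)), so the effect on the change scale is 0.80 / √(2(1 − r)). With no change in HIFT1 and 20 per arm:

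| Assumed r | SD of change (mg/dL) | d on change scale | One-sided | Two-sided | Bonferroni (df 57) |
|---|---|---|---|---|---|
| 0.3 | 29.6 | 0.68 | 68% | 55% | 38% |
| 0.5 | 25.0 | 0.80 | 80% | 69% | 53% |
| 0.7 | 19.4 | 1.03 | 94% | 89% | 79% |
| 0.8 | 15.8 | 1.26 | 99% | 97% | 93% |

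**4. The HIFT1 assumption.** The 15% is described as a change within HIFT3. It equals the HIFT3–HIFT1 difference only if HIFT1, which also trains, does not change. For illustration, suppose HIFT1 improves by 5% (assumed) and the SD of change is 25 (r = 0.5). Then d = 0.80 − (0.05 × 129)/25 = 0.80 − 0.258 = 0.542, and two-sided power is 39%.

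**The case against.** Three objections have weight.

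**Sidedness.** A reader might infer that using a paired test by itself takes power from 90% to 69%. It does not. At the protocol's own one-tailed α, replacing the paired test with an independent one gives about 80%. Reaching 69% also needs the move to a two-sided test. That move is justified, because the analysis plans a non-directional F-test and names no one-tailed test, but it is a second correction.

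**Certainty.** A reader might also infer that the trial cannot have 90% power. The document does not support that. It gives neither the SD of change nor the pre-post correlation. If d refers to the baseline SD and r is about 0.7 to 0.8, two-sided power is 89% to 97%, provided HIFT1 does not change. This stands, and it limits the conclusion to a claim that is unsupported.

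**Exploratory label.** The trial calls itself exploratory and plans effect sizes and confidence intervals for all outcomes, which softens the risk of misreading a null result. That is fair, but the section still states 90% power and promises superiority, and the label does not make the calculation fit the claim.

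Reading "paired" as a slip for "independent" does not help: no independent-groups version at d = 0.80 gives 20.

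**Conclusion.** The point holds in this form. The sample size rests on a within-subject test, while the claim and the planned analysis are between independent arms; and the inputs as written give 15, not 20.

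Taking d = 0.80 on the change scale, 20 per arm gives about 80% power at the stated one-sided 0.05, 69% two-sided and 52% under the planned F-test then Bonferroni. None of these is 90%.

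On the baseline-SD reading, which is inferred, two-sided power runs from about 55% (r = 0.3) to 97% (r = 0.8) and assumes no change in HIFT1. The document supplies nothing that would place the trial within that range.

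**What to change.** In Sample size {14}:

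1. Replace the paired one-tailed calculation with a between-arm calculation matched to the analysis in {20a}, and state the sidedness.
2. Keep 20 per arm, but restate the power: at d = 0.80 on the change scale, about 69% for a two-sided comparison and about 52% for the planned Bonferroni contrast, with 90% two-sided power only at d of about 1.05.
3. State the SD of 12-week change, or the pre-post correlation, from the pilot and cited data. If these support a larger effect on the change scale, recompute from them.
4. State the ApoB change assumed in HIFT1, so that d is a difference between arms.
5. Remove the wording that the sample "will establish the superiority of HIFT3 versus HIFT1 for pre- to post-differences in the primary outcome ApoB".

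The cost is a revised paragraph and, unless the SD of change proves favourable, a lower stated power. No extra participants are required.

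### The 0.90 power for HIFT3 versus HIFT1 on ApoB comes from a paired one-tailed test; with 20 per independent arm and d = 0.80 it is 0.80 one-tailed or 0.69 two-tailed, and about 0.52 after the planned Bonferroni adjustment

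*Protocol article*

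**What the plan says.** All of this comes from the protocol article.

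- **Sample size {14}.** The main outcome is change in ApoB between HIFT1 and HIFT3, and the calculation "assumed a 1:1 equal allocation between HIFT1 and HIFT3". The inputs are: "Assuming a power of 0.90, *α* = 0.05, and an effect size of *d* = 0.80". From these, a "paired samples one-tailed *t*-test sample size calculation revealed a sample size of 60 subjects (20 per group"), which "will establish the superiority of HIFT3 versus HIFT1 for pre- to post-differences in the primary outcome ApoB". Recruitment continues until 20 per arm have completed.
- **Trial design {8}.** The trial is a "parallel-group, three-arm, exploratory, randomized, dose-response clinical trial".
- **Statistical methods {20a}.** Paired t-tests are assigned to pre-post change within each group. For the comparison between arms: "A one-way ANOVA will be used to compare the primary and secondary outcomes pre-post mean change between the three groups". The significance level is p ≤ .05, and a significant F is followed by Bonferroni-adjusted post hoc comparisons. No one-sided between-group test is mentioned there.

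**The concern.** The sizing claim concerns a difference between two randomised arms, but the test named is a within-person one. A paired test has a single sample of differences. The contrast between arms carries the sampling variance of both arms, so at the same standardised effect it needs about twice as many people in each arm. The protocol draws this distinction itself in the analysis section but not in the sample size section.

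The sidedness does not match either. The calculation is one-tailed, while the planned comparison is a non-directional F test followed by Bonferroni tests.

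The trial looks for the smallest effective weekly dose. A non-significant HIFT3-HIFT1 result could easily be taken to mean that one session is as good as three. A reader relying on the stated power would put the chance of missing d = 0.80 at 10%. On independent arms it is about 20% one-tailed, 31% two-tailed, and 48% after the planned adjustment.

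**Working it through.** **Inputs.** d = 0.80, alpha = 0.05, power = 0.90 and 20 per group (Sample size {14}); parallel arms at 1:1:1 (Trial design {8}); ANOVA on change with Bonferroni post hoc tests (Statistical methods {20a}). All powers use the exact noncentral t or F distribution.

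**Step 1: the plan's own figure.** For a paired test, df = n − 1 and the noncentrality is d√n.

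| Paired test, d = 0.80 | Smallest n for 0.90 | Power at n = 20 |
|---|---|---|
| One-tailed (as stated) | 15 (noncentrality 0.80 × √15 = 3.10; power 0.903) | 0.964 |
| Two-tailed | 19 (noncentrality 0.80 × √19 = 3.49; power 0.909) | 0.924 |

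The stated inputs give 15, so the figure of 20 is not reproduced.

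**Step 2: independent arms, unadjusted.** Here df = 2n − 2 and the noncentrality is d√(n/2). With n = 20 that is df = 38 and 0.80 × √10 = 2.53.

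| Independent arms, d = 0.80 | Critical t at n = 20 | Power at 20 per arm | n per arm for 0.90 |
|---|---|---|---|
| One-tailed 0.05 | 1.686 | 0.799 | 28 |
| Two-tailed 0.05 | 2.024 | 0.693 | 34 |
| Two-tailed 0.05/3 (Bonferroni, three pairs) | 2.505 | 0.516 | 44 |

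Pooling the error over all three arms (df = 57) raises the Bonferroni figure only to 0.529.

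**Step 3: the planned F test.** With 20 per arm, df = 2 and 57, the critical F is 3.159, and the noncentrality is 20 × Σ(mᵢ − m̄)², with means in SD units and HIFT1 and HIFT3 0.80 apart.

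- HIFT2 midway (0, 0.40, 0.80): the sum of squares is 0.320, the noncentrality 6.40 and the power 0.589.
- HIFT2 equal to one extreme (0, 0, 0.80): the sum of squares is 0.427, the noncentrality 8.53 and the power 0.723.

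**Step 4: the effect that 20 per arm detects with 0.90 power.** Solving Step 2 for d gives about 0.94 one-tailed and 1.05 two-tailed, unadjusted.

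**Step 5: why these cannot be turned into mg/dL.** The protocol gives a baseline SD of 25 mg/dL around a mean of 129, not an SD of change. If the pre and post SDs are equal with correlation r (an assumption), the SD of change is 25√(2(1 − r)).

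- r = 0.5: the SD is 25, and the detectable differences are 0.942 × 25/129 = 18% and 1.052 × 25/129 = 20%.
- r = 0.8: the SD is 15.8, and they are 0.942 × 15.8 = 14.9 mg/dL (12%) and 1.052 × 15.8 = 16.6 mg/dL (13%).

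The answer moves across the protocol's 15% depending on a quantity the document does not give.

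**The case against.** **Two-sidedness is inferred.** No section uses the term. The sample size section says one-tailed, and the research hypothesis of a dose-response is directional. This stands. Correcting only the undisputed error, paired to independent, and keeping the declared one-tailed alpha gives 0.80. A reader might take 0.69 as the single true power. The documents do not support that, because 0.69 depends on preferring the non-directional ANOVA to the declared one-tailed test. It is also not the power of the planned analysis, which is an F test followed by Bonferroni comparisons.

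**Paired may only mean that change scores are used.** Comparing change scores between two arms is still an independent-groups test, so Step 2 applies.

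**The figure of 20 may have another origin.** It lies close to a paired two-tailed test at 0.90 (19), but also close to an independent one-tailed test at 0.80 (power 0.799 at 20 per arm). A reader might infer which calculation was really run; the document does not settle this.

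**The trial may seem unable to detect its 15% effect.** This inference does not hold either. Step 5 shows that it reverses with the assumed correlation. The 15% is also a reduction within HIFT3, not a difference between arms.

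**The trial is labelled exploratory.** True, and that is a reason not to demand more participants. It does not excuse a stated power of 0.90 and a promise of superiority that belong to a different test.

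**Conclusion.** The point holds. The sample size section names a test that does not fit the contrast it is said to power, and its inputs do not return its n. With d = 0.80 and 20 per independent arm, power is about 0.80 one-tailed or 0.69 two-tailed without adjustment. It is 0.59 to 0.72 for the three-group F test and about 0.52 for the Bonferroni-adjusted HIFT3-HIFT1 comparison. The stated 0.90 is not reached on any of these readings.

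The assumptions are as follows.

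- d = 0.80 is taken as given and read as the HIFT3-HIFT1 difference in change divided by the SD of change.
- HIFT2 lies between the other two arms or equals one of them.
- Bonferroni covers three two-sided pairs.
- 20 per arm are analysed. The protocol secures 20 completers, but its analysis section keeps only those with at least 80% of the intervention and unchanged diet and activity, so the per-protocol number could be lower.

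The error lies in the stated test and power. It does not show that the trial must enlarge.

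**What to change.** In Sample size {14}, keeping n:

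1. Replace the paired test with an independent-groups comparison of ApoB change between HIFT3 and HIFT1.
2. Reconcile the one-tailed alpha with the non-directional ANOVA and Bonferroni tests in Statistical methods {20a}. The choice of sidedness is the sponsor's, but both sections must state the same one.
3. Replace the promise to establish superiority with neutral wording such as *will compare*.
4. Restate the power, for example: *With 20 analysed per arm and d = 0.80 for the HIFT3-HIFT1 difference in ApoB change, an unadjusted independent-groups comparison has about 80% power one-sided or 69% two-sided, and about 52% with the planned Bonferroni adjustment; 90% unadjusted power needs d of about 0.94 one-sided or 1.05 two-sided.* Once sidedness is settled, keep only the figures that apply.
5. Give no detectable difference in mg/dL or percent unless an SD of change is supplied.

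The cost is one paragraph of wording and a less favourable stated power. Recruitment, conduct and the number of participants do not change.

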#### Recruitment {15}

Participants will be recruited via advertisement flyers posted in the communities of Gunnison County, social media, word of mouth, employee email lists of WCU and GVH, local newspaper and magazine ads, churches, and through physician referral among the Gunnison County health care providers. To account for the logistical capacity of data collection, participants will be recruited in cohorts of 12 (randomized into intervention groups) where each cohort will complete the entire study before the next cohort begins. This will continue until 20 participants per intervention group have completed data collection.

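### The sample size and recruitment stop count study completers, but the main analysis rule admits only adherent completers, and the plan does not say which analysis set the 20 per arm refers to

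*Protocol article*

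**What the plan says.** Four places in the protocol article bear on this.

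- **Sample size {14}.** The calculation targets ApoB for HIFT3 versus HIFT1 and arrives at 20 per group. The allowance is "With an estimated 5% dropout rate, we will recruit 22 subjects/group to obtain the necessary sample size of 60". Cohorts are then added until 20 per group have finished the study.
- **Recruitment {15}.** The same stop is tied to data collection: "This will continue until 20 participants per intervention group have completed data collection".
- **Statistical methods for primary and secondary outcomes {20a}.** The section opens by restricting the data: "Only data from participants who complete ≥ 80% of total exercise intervention and with no noticeable change in eating" or in physical activity habits are included.
- **Methods for non-adherence and missing data {20c}.** If non-adherence occurs, outcomes are tested in two sets. One is an intention-to-treat set of everyone randomised. The other is a per-protocol set defined by the 80% criterion alone, without the diet and activity condition. Neither is named as primary, and a later sentence leaves open whether intention-to-treat is appropriate.

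**The concern.** The number that closes recruitment and the number that enters the analysis are defined differently. A participant can attend post-testing, count toward the 20, and then be removed for attending under 80% or for a change in diet or activity. Nothing in the plan replaces that person, and the 5% allowance covers only people who leave.

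At stake is what the stated sample size refers to. If {20a} governs, the 20 per arm is an upper limit for any arm that stops at exactly 20 completers. If the all-randomised set governs, the 20 is met. The plan does not say which. The restricted set is also selected on behaviour after randomisation, and that behaviour may differ by dose, so the choice affects bias as well as precision.

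This is separate from the conflict in {14} between 22 per group (66) and a total of 60. It would remain if exactly 20 per arm completed.

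**Working it through.** **1. The plan's own inflation.** 20 / (1 − 0.05) = 21.05, rounded up to 22 per group. The 22 is reproduced with dropout as the only loss, so nothing in it covers completers who fail the adherence rules.

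**2. What the 80% rule demands.** The documents do not define the 80% as a session count; I read it that way. Twelve weeks at 1, 2 and 3 sessions give 12, 24 and 36 sessions. Rounding 80% up gives 10 of 12, 20 of 24 and 29 of 36.

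**3. Expected exclusions.** The documents give no attendance figure, so a range is needed. Assume each session is attended independently with probability p, the same in every arm. The share retained is P(X ≥ 10 | 12, p), P(X ≥ 20 | 24, p) and P(X ≥ 29 | 36, p).

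| p | Excluded HIFT1 / HIFT2 / HIFT3 | Analysed of 20 completers |
|---|---|---|
| 0.95 | 2% / 0.6% / 0% | 19.6 / 19.9 / 20.0 |
| 0.90 | 11% / 9% / 2% | 17.8 / 18.3 / 19.5 |
| 0.85 | 26% / 29% / 16% | 14.7 / 14.3 / 16.8 |

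At p = 0.90 the chance that all 20 HIFT1 completers pass is 0.889^20, about 10%. Diet and activity exclusions would add to these losses and cannot be quantified from the documents.

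**4. Power for HIFT3 versus HIFT1.** Inputs from {14}: d = 0.80, α = 0.05, one-tailed. For two independent groups the noncentrality is d / √(1/n₁ + 1/n₃) on n₁ + n₃ − 2 degrees of freedom.

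- 20 and 20: 0.80 (0.799)
- 19.6 and 20.0 (p = 0.95): 0.80 (0.796)
- 17.8 and 19.5 (p = 0.90): 0.77
- 14.7 and 16.8 (p = 0.85): 0.71

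**5. Power by the formula the plan names.** {14} specifies a paired one-tailed test, "Assuming a power of 0.90" and "an effect size of *d* = 0.80". With noncentrality d√n on n − 1 degrees of freedom, power is 0.964 at n = 20, 0.920 at 16, 0.903 at 15 and 0.882 at 14. The smallest n giving 0.90 is 15, so the named test does not yield 20. A paired two-sided test needs 19, the nearest match to 20; its power is 0.909 at 19 and 0.892 at 18.

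**6. Size of a repair by counting.** If 5%, 10%, 20% or 30% of completers were excluded, keeping 20 analysed would need 20 / (1 − e), that is 22, 23, 25 or 29 completers per arm. Allowing for 5% dropout as well, 20 / [(1 − e) × 0.95], gives 23, 24, 27 or 31 randomised per arm.

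**The case against.** **An all-randomised set already exists.** {20c} provides it in exactly the situation of concern, and it holds at least 20 per arm whenever the stop rule is met. This stands in part. The set is conditional and unranked, and {20a}, the section headed as governing the primary and secondary outcomes, restricts the data outright. The two sections must be reconciled.

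**Twenty completers is a floor.** Cohorts of 12 give about 4 per arm, so five cohorts give exactly 20. With 5% dropout the chance of no loss among 60 is 0.95^60, about 5%, so a sixth cohort is likely. If that cohort is full, 24 × 0.95 = 22.8 complete per arm, and at 90% attendance about 20.3, 20.9 and 22.3 are analysed. This stands as a reason why the shortfall may not occur. It is a by-product of cohort size: the text does not say the last cohort must be full, and at 85% attendance the same sum gives 16.8, 16.3 and 19.1.

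**The unequal exclusion depends on the model.** Participants choose among Monday, Wednesday and Friday slots, so someone with one session a week may have other days available, which could shrink or reverse the difference between arms. Part of the difference is rounding: 10/12 and 20/24 are 83.3%, and 29/36 is 80.6%. At 85% attendance HIFT2 loses most. This stands: the arm-specific figures illustrate what could happen and do not predict it.

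**The planned power is not necessarily lost.** A reader might infer that exclusions take the trial below its stated 0.90. The documents do not support this. The paired one-tailed test they name keeps 0.90 down to 15 per arm, a loss of a quarter of 20 completers.

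**Conclusion.** The mismatch is real and should be corrected. The 5% allowance and the stop rule count completers, {20a} analyses a narrower group, and {20c} does not settle which set is primary. An arm that stops at 20 completers falls below the stated 20 with one exclusion.

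The size of the effect depends on an exclusion rate that the documents do not give. Under independent attendance it ranges from negligible at 95% to a fall in between-arm power from 0.80 to 0.77 at 90% and 0.71 at 85%, before any diet or activity exclusions and with recruitment stopping at exactly 20 per arm.

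It would be tempting to conclude that fewer than 20 per arm will be analysed. That holds only if exclusions occur, the restricted set is primary and the last cohort leaves no surplus. The gap between the stated 0.90 and 0.80 at a full 20 per arm should not be charged to this point either. It comes from applying a paired formula to a between-arm question and is a separate error.

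**What to change.** Reconcile {20a} and {20c} by naming the all-randomised set as primary for the ApoB comparison of HIFT3 with HIFT1, unconditionally, and keep the at-least-80% set as supportive with one definition in both sections. The stop at 20 completers then supplies at least 20 per arm to the analysed set.

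If the restricted set stays primary, there are two options. One is to define the stop in {14} and {15} as 20 participants per arm evaluable under that set, which the sequential cohorts make feasible. The other is to state an assumed rate for attendance, diet and activity exclusions, add it to the 5%, and report power at the expected analysed number.

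Naming the primary set costs wording only. Keeping the restricted set costs further recruitment (for example 24 randomised per arm at an assumed 10% exclusion plus 5% dropout) or a less favourable stated power.
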